### Procedure

Recruitment will take place between June 2015 and December 2016. The recruitment will be through PROATA’s treatment waiting list, printed notices and broadcasting of written and oral media. The first contact will be made by the research team by phone or Email. Those who will be considered eligible for the study will be invited for a first interview at which point informed written consent will be completed, inclusion and exclusion criteria confirmed, and a medical history and physical examination including height and weight (with calibrated scale) undertaken. Medical assessment will accord with international guidelines for weight loss management. Laboratory tests will be circulating fasting lipid profile, fasting glucose matched with insulin, liver function, electrolytes, urea, uric acid and creatinine. A semi-structured interview and self-report questionnaires to determine the eating disorder and co-morbid diagnoses and suicide risk will be conducted. A second appointment will be scheduled for a semi-structured interview that confirms the eating disorder diagnosis and completes a detailed assessment of eating disorder symptoms and behaviours (as detailed in the study timeline on Table 2).

**Table 2 Tab2:** Timetable of administration of assessment measures

	Baseline	Mid-treatment	End-oftreatment	Follow-up (6 and 12 months)
Demographic questionnaire	✓			
Mini International Neuropsychiatric Interview	✓			
Anthropometry^a^	✓	✓	✓	✓
Eating Disorder Examination	✓		✓	✓
Eating Disorder Examination Questionnaire	✓	✓	✓	✓
Other self-report measures^b^	✓	✓	✓	✓
Adaptive function self-report measures^c^	✓		✓	✓
Physical state biomarkers^d^	✓		✓	
Client satisfaction and success of blinding questions			✓	✓

^a^Waist and hip circumferences, pulse and sitting blood pressure, height and weight for BMI calculation; BMI is also monitored weekly in session

^b^LOCES, BES, DASS21

^c^SF-12: ‘days out of role’

^d^Fasting blood glucose, insulin, lipid profile, liver function test, electrolytes, urea, creatinine and uric acid

*BES* Binge Eating Scale, *BMI* body mass index, *DASS-21* Depression, Anxiety and Stress Scale-21, *LOCES* Loss of Control Over Eating Scale, *SF-12* 12-item Short Form Health Survey

Single blinding will be achieved by not informing participants of any specific details of the therapy content. The information at recruitment that will be provided to participants regarding the therapy is as follows: ‘We have developed an approach that integrates techniques from cognitive behavioural therapy for eating disorders with behavioural strategies for weight loss. One is called HAPIFED (a Healthy Approach to Weight Management and Food in Eating Disorders), and the other is called cognitive behavioural therapy-enhanced … If you agree to participate in this study and have met all the inclusion criteria and if outpatient therapy is suitable for you, you will be randomly allocated (through an online programme) to a group therapy programme that will comprise twice-weekly group over about 1 month … You will have an equal chance (like tossing a coin) of participation in one or other treatment’ (translated from Brazilian Portuguese by author PH). Participants will not be informed if they will be in a HAPIFED or in a CBT-E therapy group at any point, and any treatment materials provided to participant will not be identified as being from either HAPIFED or CBT-E manuals.

Those who will be considered eligible for the study will be randomised in blocks of 20 (2 therapy groups) using an online site (www.sealedenvelope.com). One hundred participants will be allocated over 18 months to 10 groups with 10 participants in each group. Five groups will receive HAPIFED (experimental group) and five will receive CBT-E (control group). An investigator external to the site (PH) will administer the allocation which will be concealed and revealed only to trial therapists and therapy supervisors until the final participant completes follow-up.

### Description of interventions

HAPIFED has 5 stages that comprise 1 individual initial clinical assessment session (session 1) with a psychologist followed by 29 × 90-minute group office-based meetings twice weekly for 4 weeks, then weekly, with 2 psychologists over a total of 6 months. These include four conjoint sessions, two with a dietician and psychologist, one with an occupational therapist, and one psychoeducational session introducing internal hunger and satiety monitoring with a medical doctor. All conjoint sessions are within the first stage of therapy (sessions 2–11). In addition, the occupation therapist will make 2 domiciliary (home) visits (in the 5th and 13th weeks of treatment) and 1 phone call contact (between sessions 21 and 22) to each participant. The aim of these visits is to assess the environment and weight-maintaining habits within the home context. The occupational therapist will formulate a personalised behavioural change programme that will identify opportunities and propose modifications to daily routines to increase physical activity levels and improve relationships with food preparation and consumption. Where severe body image distress has prevented physical activity in front of other people, the occupational therapist will support the participant in physical activity around others and practice techniques discussed with the psychologist to use in relevant situations (e.g., how to cope with situations when feeling stigmatised). The phone call is to check progress since the home visits.

Stage 1 (sessions 2–11) begins with psychoeducation that includes information on why ‘diets’ fail, non-hungry and hungry eating, and reviewing the individual’s eating disorder, weight history, family, and medical history relevant to determining both the likelihood of gaining or losing weight with treatment and obesity-related health risks. Information about eating disorders and an introduction to the CBT formulation of the development of the eating disorder are provided. In addition to disordered eating (bingeing, attempted or actual fasting) and compensatory behaviours (e.g., fasting, vomiting, compulsive exercise), it incorporates weight history and the role of life events and mood intolerance; and, where relevant, interpersonal deficits, low self-esteem and clinical perfectionism. In-session weighing, regular eating and monitoring of key behaviours are introduced. Session 4 includes a presentation on appetite regulation and the rationale for an approach of modifying eating according to internal cues, as outlined in the book *The Don’t Go Hungry Diet* [22]. Specific steps are outlined to help participants lose weight by listening to their appetite, including hunger and satiety scores that are used to monitor and gain awareness of appetite, as well as increasing fruit and vegetable intake and physical activity. This is an alternate to a conventional weight loss programme, which is based on external measures of control (e.g., counting portion size/number) and explicit messages about restriction (e.g., reduce fat, etc.). In session 6 there is a motivational talk from the occupational therapist, and pedometers are provided to promote physical activity. The pedometer will measure the level of activity participants have in their usual routine as well as increase their awareness of their activity levels. After session 19 the pedometers are provided again to check whether they have been able to make improvements in their routine level of activity as well as a reminder of this need. The pedometers will be proposed to be used for 5 days (3 weekdays and 2 weekend days).

Stage 2 (session 12) is a brief ‘reformulation’ time and for personalisation of the formulation. Stage 3 (sessions 13–-19) has an emphasis on behavioural activation and activity monitoring while also addressing the key behaviours and training in specific behavioural skills. Monitoring of key eating and related behaviours (including binge eating, exercise and urge to exercise, other compensations such as vomiting, and body checking) continues with concomitant ratings of mood and appetite, with an additional emphasis on behavioural activation and activity monitoring. Approaches include appetite-focussed CBT techniques. Monitoring is based more on appetite cues than food monitoring. This aims to direct attention away from an excessive focus on type of food [23]. Behavioural experiments are introduced to prevent eating disorder behaviours, establish regular meal patterns and promote self-control. In this stage, nutritional education and counselling and exercise are addressed. The participants will work to make lifestyle changes to establish more healthy eating and physical activity patterns, and food choices which are less than sufficient to meet energy needs, in order to bring about modest, at least 5 %, of previous body weight loss. This is a level known to improve health outcomes [24]. Exercise is addressed using behavioural activation strategies. Stage 4 (sessions 20–27) introduces Socratic questioning and challenging of beliefs and attitudes which reinforce eating disorder behaviours, such as valuing oneself according to one’s weight and shape, and ‘all or nothing’ dichotomous thinking. Problem-solving is also incorporated here. Mood intolerance is addressed with training in specific emotion regulation skills. Behavioural experiments and the appetite-awareness and physical activity plan from phase 2 continue in this phase. Stage 5 (sessions 28–30): as in CBT, the final sessions of HAPIFED involve relapse prevention including reviewing strategies that have successfully helped. By the end of therapy, the goal is to achieve a regular pattern of eating, of varied and appropriately sized food portions, with mild to modest energy restriction. Binge eating and self-induced vomiting and other behaviours are intended to be reduced or absent, and food, eating and weight are envisaged to no longer dominate the patient’s self-view.

Four group follow-up sessions over the subsequent 6 months are also offered to participants. These sessions are conducted by the psychologists who led the group. The aim is to address relapses, review ongoing progress and promote continued improvement.

The comparison intervention is the standard leading evidence-based therapy for BN and BED, CBT-E [25–27]. In this study the broad version of CBT-E [18] with additional mood intolerance and other modules will be used and will match HAPIFED in session duration and number. There will be 1 individual session at the start of treatment plus 29 group sessions over 6-months in this RCT. CBT-E uses therapists from a single discipline, in this study, psychology. CBT for BED and BN has been used successfully in a group format [28, 29].

The structure of HAPIFED has been based on the structure of CBT-E. CBT-E [18] is organised in four stages. Stage 1 (sessions 0–-7) comprises twice-weekly appointments which aim to engage the patient with the treatment, create the formulation, provide information and introduce in-session weighing and regular eating. Stage 2 (sessions 8–9) encompasses the revision of the progress and of the formulation, trying to identify any difficulty to proceed. Stage 3 (sessions 10–17) addresses the mechanisms that maintain the symptomatology and the last stage (sessions 18–20) prepares the patient to continue the progress obtained by the treatment.

### Outcomes

The primary outcome of this intervention will be a reduced body weight sustained to 12 months after completion of the intervention. Secondary outcomes will be (i) improved metabolic indicators of weight management; (ii) reduction in eating disorder symptoms, namely binge eating, loss of control over eating, driven exercise, purging, and self-induced vomiting and dysfunctional cognitions (weight and shape overvaluation and eating concerns); (iii) being less than 1 standard deviation above the community mean for global score on the Eating Disorder Examination (EDE) [18]; (iv) improved adaptive function (‘days out of role’), physical and mental health-related quality of life (HRQoL); and (v) reduced levels of depression and anxiety.

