## Background

The combined general population lifetime prevalence of bulimia nervosa (BN) and binge eating disorder (BED) is around 5 % in women and 3 % in men [1]. Both disorders are characterised by recurrent binge eating or uncontrolled overeating episodes which, in the case of BN are also associated with regular compensatory weight control behaviours (e.g., self-induced vomiting) [2, 3]. It is now recognised that an increasing number, now around 40 % of people in the community with BN or with BED are obese [4, 5]. In clinics the prevalence is even higher, up to 80 % [6, 7]. Bulik et al. suggested, in a paper to highlight the issues of managing weight and eating disorders, that ‘BN in the overweight and obese patients may represent the natural evolution of the eating disorder on the backdrop of the obesity epidemic’ (Bulik et al., p.6) [8]. They wrote about the increase in clinical presentations of overweight and obese patients with BN and their requests for help with weight management. They argued that due to the rise in combined prevalence of co-morbid obesity and BN and BED, and their shared risk and maintaining features, an urgent need for new approaches to management is needed [8].

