## Method/Design

### Participants

This study will comprise 100 participants recruited from both community and clinics. Assessments and therapy will be conducted in the Eating Disorders Programme (PROATA) clinic in the Department of Psychiatry of the Federal University of São Paulo (UNIFESP), Brazil. The inclusion criteria are: age ≥ 18 years; either sex; a primary eating disorder diagnosis of BN or BED type according to the *Diagnostic and Statistical Manual of Mental Disorders, fifth edition* (DSM-5) and/or the proposed *International Classification of Diseases, eleventh version* (ICD-11) criteria [2, 3]; and a body mass index (BMI) ≥ 27 and < 40 kg/m^2^. The exclusion criteria are: a current diagnosis of psychosis or bipolar disorder and/or a high level of suicide risk; use of weight loss medication; history of bariatric surgery; clinical conditions that interfere with appetite regulation (e.g., Prader-Willi and Cushing syndromes); and currently receiving psychological treatment for eating disorders.

The present study *a priori* power analysis was based on the estimate of a moderate between group effect size (i.e., 0.6) in the primary outcome of weight loss. To achieve this with power of 0.8 and 1-tailed alpha *p* < 0.05, a minimum of 36 participants per group is required according to Cohen’s tables. Allowing for attrition the sample size is 50 per arm and 10 per therapy group.

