### Assessment

Participants will be assessed 4 times: at baseline, 6 months (end of therapy), 12 months (6 months after end of therapy) and 18 months (1 year after end of therapy). Assessments will be conducted on all participants including those who do not complete treatment.

The timing of administration of assessment measures is shown in Table 3.Measures administered only at baseline:1.1.A self-report questionnaire will be used to assess sociodemographic and clinical variables (age, gender, race, occupation, marital status, education, eating disorder onset and lifetime history of eating disorders) and will include a specific questionnaire to determine income status, namely the ‘Critério de Classificação Econômica Brasil 2014’ [30].1.2.Mini International Neuropsychiatric Interview (MINI). The MINI is a reliable and valid structured interview for psychiatric diagnoses according to the DSM [2]. Only the MINI-5 [31] for DSM-IV [32] is translated into Portuguese. Thus, the MINI-5 will be used in this study, with modifications to the coding of all disorders to accord with DSM-5 diagnoses as in the MINI-7 [33].Measures repeated from baseline to 12-month follow-up:2.1.Anthropometry will include waist and hip circumferences (mean of 3 measures), pulse and sitting blood pressure. Height and weight will be measured with a stadiometer and calibrated scale, from which BMI (kg/m^2^) will be calculated.2.2.Eating disorder psychopathology instruments:2.2.1.Eating Disorder Examination Edition 17.0D [34]: the EDE is the ‘gold standard’ semi-structured interview used to assess eating disorder symptoms and diagnoses. Four subscales can be derived measuring severity of dietary restraint, eating, shape and weight over concern. These are averaged for a global score. Version 16.0 [18] of the EDE was translated to Brazilian/Portuguese by collaborators from the Federal University of Rio de Janeiro ([name] and [name]), by authors of this paper (MAP, AC) and by a PROATA eating disorder specialist ([name] – CM), back-translated to English by a certified translator and the final version approved by one of the authors of EDE ([name]). The reliability and concurrent validity of the translated EDE was tested and found to be satisfactory. There was 80 % inter-interviewer agreement (kappa 0.69) on the diagnosis made with the EDE interview and 77.3 % agreement (kappa 0.68) (unpublished data provided by author AC). The diagnosis was made according to the eating disorder module of the Structured Clinical Interview for DSM-IV Axis I Disorders-Patient Edition (SCID-I/P) interview [35] (Portuguese version) [36]. Small adjustments were made by the author MAP, so that the Portuguese version used in the study is now consistent with the 17th version of the EDE [34], in order to derive DSM-5 diagnoses.2.2.2.Eating Disorder Examination Questionnaire (EDE-Q) [37]: a self-report measure is derived from the EDE interview. Like the EDE, it has four subscales (dietary restraint, eating, weight and shape concerns). An unpublished Brazilian/Portuguese translation of the more recent 28-item version of the EDE-Q (V. 6.0) [18] was prepared by CM and MAP, and this version will be used. This translation utilised the validated European Portuguese version of the original 36-item EDE-Q [38], which was then modified to be consistent with Brazilian/Portuguese.2.2.3.Loss of Control over Eating Scale (LOCES) [39]: a 24-item self-report that examines the presence of loss of control during the binge eating episodes in the last 4 weeks. A Brazilian/Portuguese translation and assessment of psychometric properties (factor analysis and convergent validity) has been completed ([name] et al., manuscript submitted).2.2.4.Binge Eating Scale (BES) [40]: a 16-item self-report instrument that has been translated and validated in a Brazilian sample [41]. This scale evaluates the presence and severity of binge eating. It has adequate psychometric properties in the Brazilian version, with a cut-off point of 17 for the screening of eating disorders in obese individuals seeking treatment for weight loss.2.3.General psychopathology instrument:2.3.1.Depression, Anxiety and Stress Scale (DASS-21) [42, 43] in a translated and validated Brazilian/Portuguese version [44]. This self-report instrument measures the presence and severity of depressive symptoms, anxiety and stress.2.4.Adaptive function:2.4.1.Health-related quality of life will be measured with the 12-item Short Form Health Survey (SF-12) [45]. This is a self-report questionnaire that measures health-related quality of life, subdivided in 2 scales – Physical Health Component Summary scales (PCS) and Mental Health Component Summary scales (MCS). A score lower than 30 on the MCS indicates severe impairment in mental health, and a score from 31 to 40 indicates moderate impairment. This is a widely-used measure with sound psychometric properties and has been translated into Brazilian/Portuguese [46].2.4.2.Disability will be assessed using a question analogous to the ‘days out of role’ questions employed in the Australian National Survey of Mental Health and Well-Being [47]. Participants will be asked to record the number of days after the following question: *During the past 4 weeks, on how many days, if any, were you unable to complete your work, study or household responsibilities because of any problem with your (physical or emotional) health?* This was translated by the author MAP.Measures only at baseline and end-of-treatment.The following medical pathology tests will be performed at baseline and end-of-treatment only: fasting circulating glucose, insulin, lipid profile, liver function test, electrolytes, urea, creatinine and uric acid.Measures at end-of-treatment only.4.1.Client/patient satisfaction questionnaire [48]. This eight-item scale assesses general satisfaction with services. It has a high internal consistency (*α* = 0.93) and correlates with therapist’s assessment of client satisfaction and with early treatment drop out. This was translated by the author MAP.4.2.Participants will be asked which group, experimental or control, they thought they were in. When all participants have completed 12-month follow-up and data has been processed, participants will be debriefed, and full information will be provided about HAPIFED and CBT-E.

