### Data collection, management and analysis

Researchers conducting outcome data entry will be blind to the study group of participants. Between-group outcome analyses will not begin until after the final 1-year follow-up. Governance of data and an independent Data Monitoring Committee (DMC) responsible for interim mid-point in recruitment safety and futility analyses of de-identified data will be conducted at the University of Western Sydney site. The DMC will be composed of a biostatistician with expertise in RCTs, and two senior independent clinical researchers with expertise in RCTs. The trial will be discontinued if assessed to be futile and/or participants’ binge eating is increasing significantly and/or attrition is over 50 %. Therapists under supervision who are not blind to treatment arm will be responsible for the safety of individual participants and will receive directly any concerns about an individual from the DMC.

STATA (StataCorp, College Station, TX, USA) for most statistics will be used. Baseline univariate between-group tests will be done to compare groups on outcome variables, clinical and demographic data. Data will be analysed following ‘intention-to-treat’ principles. Generalised estimating equations [49] with a logit response function will be used for dichotomous outcomes, such as achieving a 5 % reduction in body weight. Linear mixed effects modelling [50] will be used to test for between-group differences in the continuous outcome measures, namely weight loss, levels of ED symptom change, adaptive function, quality of life, depression and anxiety levels, waist circumference, blood pressure, and biochemical markers such as circulating lipid or glucose levels. Putative covariates will be diagnostic group (BN or BED) and use of psychotropic medication. Predictors of outcomes at 6-month and 12-month follow-up to be tested will include the rate of early (by mid-treatment) reduction in binge eating.

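### Secondary outcome (iii), an EDE global score below a cut-off, can already be met at entry, which raises the success rate in both arms and dilutes the difference between them

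*Protocol article*

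**What the plan says.** All references are to the protocol article.

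- **Outcomes.** Secondary outcome (iii) is "being less than 1 standard deviation above the community mean for global score on the Eating Disorder Examination (EDE"). The other secondary outcomes are worded as improvement or reduction; this one is a state, and nothing requires the participant to have been above the cut-off beforehand.
- **Participants.** The eating-disorder entry criterion is "a primary eating disorder diagnosis of BN or BED type according to the" DSM-5 and/or proposed ICD-11. Age, BMI and exclusion criteria are added, but no minimum EDE global score.
- **Assessment.** On the EDE: "Four subscales can be derived measuring severity of dietary restraint, eating, shape and weight over concern". The global score is their average. Also: "Assessments will be conducted on all participants including those who do not complete treatment".
- **Procedure, Table 2.** The EDE is given at baseline, end of treatment and both follow-ups.
- **Data collection, management and analysis.** Generalised estimating equations "with a logit response function will be used for dichotomous outcomes". The putative covariates are diagnostic group and psychotropic medication. Baseline EDE is not among them. Univariate tests will compare the groups on outcome variables at baseline.
- **Purging.** Outcome (ii) seeks "reduction in eating disorder symptoms, namely binge eating, loss of control over eating, driven exercise, purging, and self-induced vomiting" and dysfunctional cognitions in the whole sample. The Background describes binge eating as common to both disorders, which "in the case of BN are also associated with regular compensatory weight control behaviours".

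**The concern.** The diagnosis that admits a participant and the score that defines success measure different things. By the Background, both disorders are characterised by recurrent binge eating. The EDE global score averages restraint and concerns about eating, shape and weight. A qualifying diagnosis therefore does not guarantee a score above the cut-off. Anyone who starts below it and does not change is recorded as having reached the outcome.

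Two uses of the result are at stake. The Discussion expects the trial to inform the sample size of later trials, including on whether HAPIFED matches CBT-E for eating disorder symptoms. Inflated rates and a shrunken difference would carry into that planning and make the arms look more alike than they are. The article's second aim is the safety of adding weight loss management, and a single pooled status hides who moved in which direction.

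Outcome (ii) has a milder form of the same feature. Regular compensatory behaviour is attributed to BN, so a whole-sample mean change in purging or vomiting averages in participants with little to reduce.

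**Working it through.** **The plan's own figures.** No figure is attached to outcome (iii). The stated sample size, which concerns weight loss, does reproduce. For an effect size of 0.6, one-tailed 0.05 and power 0.8, the normal approximation gives 35 per group and the t-test solution is 35.04, rounded up to the stated 36. It is used here only for the 50 per arm.

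**Effect on the rates.** Let f be the share below the cut-off at baseline. Let p be the proportion of the others who get below it, and assume those already below stay there.

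- Observed rate = f + (1 − f) × p
- Observed difference = (1 − f) × (difference among those at or above at baseline)

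The documents give neither f nor p. With p assumed to be 60% and 40%:

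| f | Higher arm | Lower arm | Difference |
|---|---|---|---|
| 0% | 60% | 40% | 20 points |
| 10% | 0.10 + 0.90 × 0.60 = 64% | 0.10 + 0.90 × 0.40 = 46% | 18 |
| 20% | 0.20 + 0.80 × 0.60 = 68% | 0.20 + 0.80 × 0.40 = 52% | 16 |
| 30% | 0.30 + 0.70 × 0.60 = 72% | 0.30 + 0.70 × 0.40 = 58% | 14 |

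**Without the staying-below assumption.** In general, observed difference = (1 − f) × D1 + f × D2. D1 is the arm difference among those at or above the cut-off at baseline, and D2 is the arm difference in the share of the others still below it. Dilution needs only D2 = 0. If D2 is not zero, the pooled figure mixes improvement with deterioration, so the two groups should be seen separately.

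**Effect on power.** Illustration with 50 per arm, two-sided 0.05, and 60% versus 30% assumed among those at or above the cut-off:

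| f | Whole-sample rates | Power, whole sample | Power, restricted to those at or above at baseline |
|---|---|---|---|
| 0% | 60 / 30 | 87% | 87% |
| 10% | 64 / 37 | 78% | 83% |
| 20% | 68 / 44 | 68% | 78% |
| 30% | 72 / 51 | 58% | 72% |
| 40% | 76 / 58 | 48% | 65% |

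In this illustration restriction gains power although it uses fewer people (50 × (1 − f) per arm).

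**Purging and vomiting.** Let a share b of n participants per arm have BN, with arm difference d and standard deviation s in BN, and let change in BED be zero (an assumption).

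- BN only: z = d / (s × √(2/(bn))) = (d/s) × √(bn/2).
- Pooled, with diagnosis as covariate: the estimate is b × d and the residual variance about b × s², so z = bd / (s × √(2b/n)) = (d/s) × √(bn/2).

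The two agree, apart from a small extra residual term because the effect differs by diagnosis. The covariate thus protects most of the power. The pooled mean is still b × d: half the change in BN if b = 50%, 30% of it if b = 30%. The documents do not give b.

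**The case against.** **A status comparison between randomised arms is valid.** This stands. A reader might infer that outcome (iii) is biased towards HAPIFED or CBT-E. It is not: baseline status is balanced in expectation, so both rates rise and the difference shrinks. The article also does not call this outcome recovery.

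**Such detail may belong in an analysis plan that is not shown.** This stands in part. How baseline enters the model could be left there. But the article itself fixes the form of the outcome and names covariates, and neither deals with baseline EDE.

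**Baseline comparisons on outcome variables are already planned.** They are, and they may show how the arms compare at entry. They do not remove the dilution.

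**Restricting the analysis has a hidden cost.** This stands. A participant who starts below the cut-off and is pushed above it would vanish from a restricted analysis, while the whole-sample status counts that person as not meeting the outcome. Given the safety aim, restriction alone would be the wrong remedy.

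**The purging point is easily overstated.** This also stands. A reader might infer that participants with BED have nothing to reduce and that pooling destroys the analysis. The Background ties only regular compensatory behaviour to BN and does not say that BED involves none. The diagnostic-group covariate, if used, keeps most of the power. Purging is also one of several listed symptoms, many shared by both diagnoses.

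**Conclusion.** The point holds for outcome (iii). As written, a participant already below the cut-off at entry counts as a success without change. The result is an inflated rate in both arms and a diluted difference, with no bias towards either arm.

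The size is unknown. Under the assumed 60% versus 40%, with those below staying below, each 10% of the sample already below costs 2 of the 20 points. At 10% that is slight; at 30% the difference is 14 points and the rates read 72% and 58%. The documents do not support any claim that many participants will start below the cut-off, only that they can.

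The primary weight outcome and the sample size are unaffected. For purging and vomiting the remaining point is minor and concerns reporting: a pooled mean understates the change among those who have the behaviour.

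**What to change.** Leave the entry criteria as they are and change the analysis of outcome (iii):

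1. Make the main analysis the move to below the cut-off among randomised participants at or above it at baseline. Baseline status precedes randomisation, so the comparison stays randomised. Alternatively, keep the whole sample and adjust the model for baseline EDE global.
2. Report by arm how many were already below the cut-off at entry and how many of them later rise above it.
3. Keep the whole-sample status as a supporting result.
4. For purging and vomiting, keep the diagnostic-group covariate. Also report change among participants with the behaviour at baseline, and new onset among the others as a separate worsening outcome.

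The cost is wording only. Table 2 already schedules the EDE at baseline and at every later point needed, so no visit or measure is added. The downside is that fewer participants contribute to the restricted secondary analyses.
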